# LIST OF ABBREVIATIONS AND DEFINITIONS OF TERMS

| **Abbreviation/Term** | **Definition/Explanation** |
| --- | --- |
| ALT | alanine aminotransferase |
| AP | anteroposterior |
| ASA | American Society of Anesthesiologists |
| AST | aspartate aminotransferase |
| CA19-9 | carbohydrate antigen 19-9 |
| CA72-4 | carbohydrate antigen 72-4 |
| CEA | carcinoembryonic antigen |
| CI | confidence interval |
| CRFs | case report forms |
| CRP | C-reactive protein |
| CT | computed tomography |
| DFS | disease-free survival |
| EBUS | endobronchial ultrasound |
| ECG | echocardiography |
| EORTC QLQ-C30 | the European Organization for Research and Treatment of Cancer Quality of Life Questionnaire |
| EORTC QLQ-LC13 | the European Organization for Research and Treatment of Cancer Quality of Life Questionnaire in Lung Cancer |
| EQ-5D | the European Quality of Life 5 Dimensions |
| ERAS | enhanced recovery after surgery |
| FDG | fluorodeoxyglucose |
| FEV1 | forced expiratory volume in one second |
| FEV1/FVC | forced expiratory volume in one second/forced vital capacity |
| FVC | forced vital capacity |
| GCP | good clinical practice |
| Hb | hemoglobin |
| HRQoL | health-related quality of life |
| ICF | informed consent form |
| ICS | intercostal space |
| IQR | interquartile range |
| IRB | institutional review board |
| ITT | intent-to-treat |
| LN | lymph node |
| LYM | lymphocyte count |
| MVV | maximal voluntary ventilation |
| NRS | numeric rating scale |
| NSCLC | non-small cell lung cancer |
| NSE | neuron-specific enolase |
| OS | overall survival |
| PET/CT | positron emission tomography/computed tomography |
| PLT | platelet count |
| PP | per-protocol |
| RATS | robotic-assisted thoracic surgery |
| SD | standard deviation |
| VAS | visual analog score |
| VATS | video-assisted thoracic surgery |
| WBC | white blood cell count |
| WHO | World Health Organization |

# 1. PROTOCOL SUMMARY

## 1.1 Synopsis

**Protocol Title**

Safety and Feasibility of Surgery After Conversion Therapy for Locally Advanced and Advanced NSCLC.

**Objective**

The aim of this study is to evaluate the safety and feasibility of conversion surgery after induction therapy for locally advanced and advanced non-small cell lung cancer (NSCLC).

**Endpoints**

| Endpoints | Definition |
| --- | --- |
| Primary endpoints |  |
| Perioperative morbidity | The percentage of patients who have perioperative complications, mainly include: pneumonia, arrhythmia, incision infection, vocal cord paralysis, trachea cannula |
| Main secondary endpoints |  |
| Lymph nodes count | Overall lymph node counts, number of stations dissected, and number of lymph nodes in each lymph node station |
| R0 rate | The percentage of patients who achieve R0 resection. R0 is a curative resection with negative resection margins. |
| Operation time | The time from skin incision to skin closure. |
| Blood loss | The volume of blood lost in the operation. |
| Operative complications | The rate of conversion to open surgery in the operation |
| Postoperative hospital stay | Postoperative hospital stay measures the length of time elapsed between a patient’s date of surgery and discharge. |
| 30-day mortality | Death within 30 days of the surgical procedure, including patients who die after discharge from hospital. |
| 1-year overall survival (OS) | The percentage of patients who are still alive 3 years after intervention. |
| 3-year overall survival (OS) | The percentage of patients who are still alive 3 years after intervention. |
| 1-year disease-free survival (DFS) | The percentage of patients who are still alive without any evidence of disease 1 years after randomization. |
| 3-year disease-free survival (DFS) | The percentage of patients who are still alive without any evidence of disease 3 years after randomization. |

**Overall Design**

This is a single-arm, prospective study (ClinicalTrials.gov number, NCT04945928) to evaluate the safety and feasibility of conversion surgery after induction therapy for locally advanced and advanced non-small cell lung cancer.

**Design Outline**

***Patients***

| Inclusion criteria | Exclusion criteria |
| --- | --- |
| 1. Volunteer to participate in the study with good compliance. Able to complete the observation and follow-up and have signed the informed consent; 2. More than 18 years old with no limit of sex; 3. Pathologically confirmed (tumor lesion) T4N0-3 or T1-3N2-3 NSCLC with residual tumor after first-line treatment (first-line chemotherapy, targeted therapy, immunotherapy, chemotherapy combined with immunotherapy, etc.) evaluated operable for radical resection; pathologically confirmed stage IVA NSCLC evaluated operable after first-line treatment (first-line chemotherapy, targeted therapy, immunotherapy, chemotherapy combined with immunotherapy, etc.); 4. ASA score: I-III; 5. Cardiopulmonary functions meet the requirements of radical operation for lung cancer with normal liver and kidney functions. | 1. Serious heart, lung, liver and kidney dysfunction and unable to tolerate the operation; 2. Neurologic, mental illness or mental disorder which is hard to control, poor compliance, unable to cooperate or describe the treatment response; 3. Unable to receive radical resection; 4. Need of palliative or emergency operation due to lung abscess or hemoptysis; 5. Having received neoadjuvant chemoradiotherapy. |

***Sample size***

Regarding the exploratory nature of this study, a sample size of 30 patients was determined.

***Participant Group/Arm***

Participants with locally advanced or advanced NSCLC who received first-line treatment have been evaluated as resectable after multidisciplinary discussion involving the department of thoracic surgery, respiratory medicine, radiology, and oncology.

***Intervention/Treatment***

Participants having been evaluated as operable after receiving first-line treatment (first-line chemotherapy, targeted therapy, immunotherapy, chemotherapy combined with immunotherapy, etc.) will receive conversion surgery.

***Statistical Analysis***

Continuous variables which is normally distributed will be presented as mean ± standard deviation, and Student’s t-test will be used for comparison in subgroup analysis. In cases of non-compliance, continuous variables will be presented as median (interquartile range), and compared by Wilcoxon rank-sum test between subgroups. Categorical variables were presented as frequency with percentage. The test level between the subgroups will be set at α=0.05 (bilateral), and differences with P <0.05 will be considered to be statistically significant.

## 1.2 Schema

# 2. INTRODUCTION

Lung cancer is the leading cause of cancer death worldwide^1^. An estimated 2.2 million new lung cancer cases occurred in 2020, accounting for about 11.4% of total cancer diagnoses. NSCLC is the dominant type of lung cancer^2^. Approximately 80% of patients with NSCLC present with either metastatic or locally advanced disease that is not initially amenable to resection^3^.

Treatments for locally advanced NSCLC, stage III NSCLC, is controversial. Surgical resection is primarily recommended for T1-3 diseases with single station and non-bulky N2, while other stage III NSCLC are determined initially unresectable. Previous studies have shown that conversion surgery after induction therapy could bring potential benefits for these patients^4-8^. However, it requires strict operation indications and patient screening. Furthermore, this concept of treatment still needs evidence from prospective studies to prove its safety and feasibility.

This single-arm, prospective study evaluated the safety and feasibility of conversion surgery after induction therapy for initially unresectable locally advanced and advanced NSCLC patients.

## 2.1 Background and rationale for conducting this study

This study is designed to evaluate the safety and feasibility of surgery after conversion therapy for locally advanced and advanced non-small cell lung cancer.

## 2.2 Rationale for study design and study population

This is a single-center, single-arm, and prospective study evaluated the safety and feasibility of surgery after conversion therapy for initially unresectable locally advanced and advanced NSCLC patients.

Locally advanced and advanced NSCLC are stage III-IV diseases. According to the latest NCCN guidelines for NSCLC, selected T_1-3_N_2_ NSCLC patients with single station and non-bulky N_2_ can receive systemic therapy first, and if there’s no apparent progression, they may be considered to receive surgery. The T_3-4_N_1-0_ NSCLC patients may also be considered to undergo surgery, while the resectability should be well evaluated. Others are initially unresectable, and multidisciplinary treatments such as chemoradiation followed by Durvalumab and targeted therapy are recommended.

Conversion surgery is a kind of salvage surgery in a broad sense. Salvage surgery for lung cancer was first reported in 1991 for limited small cell lung cancer, which was defined as surgical resection of limited tumor after definitive medical treatment for small cell lung cancer (SCLC)^9^. Thanks to the advances in drug therapy and radiotherapy for NSCLC, conversion surgery for initially unresectable NSCLC was proposed and evaluated rapidly. This surgery is for NSCLC converted from initially unresectable to potentially resectable status because of a favorable response to induction therapy^10^.

The latest results from prospective trials of conversion surgery were all for the stage IIIA-B NSCLC. The immunotherapy plus chemotherapy was used as induction therapy. Results showed that this regimen could markedly enhance the rate of pathological complete response (pCR) with manageable toxic effects in stage IIIA-B NSCLC^4-6^.

Current reported results of conversion surgery for later stage locally advanced and advanced NSCLC were all from retrospective studies^7,8^. There continues to be a lack of evidence from prospective trials to verify its safety and feasibility. Therefore, we started this single-arm, prospective study to evaluate the safety and feasibility of conversion surgery after induction therapy for initially unresectable locally advanced and advanced NSCLC patients.

**2.2.1 Rationale for study population**

This study is a single-arm clinical trial. The aim of this study is to evaluate the safety and feasibility of salvage surgery after induction therapy for locally advanced and advanced non-small cell lung cancer. Due to the lack of previous studies for reference, the sample size is not calculated based on hypothesis testing. Regarding the exploratory nature of this study, a sample size of 30 patients was determined.

**2.2.2 Rationale for study patient**

Patients with initially unresectable NSCLC having been evaluated as operable after receiving first-line treatment are eligible for the study.

Initially unresectable clinical stage IIIA-B NSCLC is defined as T_1-3_ with multi station or bulky N_2_ and T_3-4_ N_1-0_ with invasion. All the clinical stage IIIC and IV NSCLC are initially unresectable. The Appendix 1 displays the eighth edition of the TNM classification for lung cancer.

The first-line treatments include chemotherapy, chemotherapy plus immunotherapy, and targeted therapy.

Previous studies have shown that conversion surgery after induction therapy could bring potential benefits for these patients^4-8^. Therefore, we included these patients to receive conversion surgery in our study.

## 2.3 Benefit/risk and ethical assessment

**2.3.1 Benefit assessment**

Conversion surgery after induction therapy has been shown to be a safe and feasible treatment for patients with initially unresectable NSCLC in retrospective studies. Additionally, this therapy may result in better pCR, disease-free survival (DFS), and overall survival (OS).

**2.3.2 Risk assessment**

There are disadvantages of conversion surgery after induction therapy, which could form the risks and disadvantages associated with participation in this study. The main risks for the patients are from surgery-related complications. The risks of these complications will be minimized by dedicated surgery teams. The qualifications of the responsible surgeons that participate in this study are described in section 5.2.1.

**2.3.3 Overall benefit risk conclusion**

Taking into account the measures taken to minimize risks to participants in this study, the potential risks identified in association with conversion surgery after induction therapy are justified by the anticipated benefits that may be afforded to participants with initially unresectable NSCLC.

**2.3.4 Ethical assessment**

This study will be carried out upon approval of the Institutional Review Board (IRB) in Ruijin Hospital and in compliance with the Helsinki Declaration and Good Clinical Practice (GCP) guidelines.

In keeping with the related regulations and guidelines, subjects can participate in the study only after having signed the ICF in full awareness of the objectives of the study and the risks involved and each subject has the right to withdraw from the study at any time.

We will ensure confidentiality of all patient- and study-related information and explain to the subjects the details of compensation.

# 3. STUDY OBJECTIVES, ENDPOINTS AND DEFINITIONS

**3.1 Objectives**

The aim of this study is to evaluate the safety and feasibility of conversion surgery after induction therapy for locally advanced and advanced non-small cell lung cancer.

**3.2 Endpoints and definitions**

| Endpoints | Definition |
| --- | --- |
| Primary endpoints |  |
| Perioperative morbidity | The percentage of patients who have perioperative complications, mainly include: pneumonia, arrhythmia, incision infection, vocal cord paralysis, trachea cannula |
| Main secondary endpoints |  |
| Lymph nodes count | Overall lymph node counts, number of stations dissected, and number of lymph nodes in each lymph node station |
| R0 rate | The percentage of patients who achieve R0 resection. R0 is a curative resection with negative resection margins. |
| Operation time | The time from skin incision to skin closure. |
| Blood loss | The volume of blood lost in the operation. |
| Operative complications | The rate of conversion to open surgery in the operation |
| Postoperative hospital stay | Postoperative hospital stay measures the length of time elapsed between a patient’s date of surgery and discharge. |
| 30-day mortality | Death within 30 days of the surgical procedure, including patients who die after discharge from hospital. |
| 1-year overall survival (OS) | The percentage of patients who are still alive 3 years after intervention. |
| 3-year overall survival (OS) | The percentage of patients who are still alive 3 years after intervention. |
| 1-year disease-free survival (DFS) | The percentage of patients who are still alive without any evidence of disease 1 years after randomization. |
| 3-year disease-free survival (DFS) | The percentage of patients who are still alive without any evidence of disease 3 years after randomization. |

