# 6. ASSESSMENT AND DATA COLLECTION

## 6.1 Preoperative assessments and data collection

Preoperative investigation and preparation will be accorded with the routine clinical work in the department of thoracic surgery, Ruijin Hospital affiliated Shanghai Jiao Tong University School of Medicine (see section 4.2.1).

Data collected on the randomization, eligibility and preoperative CRFs will include:

1. Personal details and demographics including height, weight, and gender;
2. Preoperative investigations performed;
3. Clinical TNM staging (the eighth edition of the TNM classification for lung cancer^12^, Appendix 1);
4. Confirmation of eligibility;
5. Confirmation of written informed consent;
6. Date of randomization;
7. Known concomitant diseases and co-morbidities;
8. Smoking status (smoking index (number of cigarettes smoked per day multiplied by years of tobacco use) is used to evaluate the smoking status of the patient).

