## 6.2 Operative assessments and data collection

The part of operative information in the CRFs will be completed. This collects data relating to the operation including:

1. Surgeon;
2. ASA status;
3. Thoracoscopic technique (robotic-assisted or video-assisted);
4. Whether there is an intraoperative change of surgical plan (inappropriateness for minimally invasive lobectomy based on intraoperative exploration, such as sublobar resection for a small lesion or extensive lung resection for a massive tumor);
5. Duration of operation;
6. Whether outcome of operation curative, palliative or unresectable;
7. Whether conversion to open surgery occurred, and reason;
8. Any intraoperative complications.

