## 6.5 Follow-up assessment and data collection

Follow-up data will be collected every 6 months after surgery until patient death or the completion of the study.

Data collected will include:

1. Patient status (alive or dead) and details of death, including:

- Date of death
- Reason of death (NSCLC related or other)

1. Details of any adjuvant therapy;
2. Details of any local or distant recurrence, including:

- Date of recurrence
- Site of recurrence
- Method of diagnosis
- Treatment for recurrence

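### DFS is timed from a randomisation that a single-arm trial does not have, and patients left with disease after surgery have no event rule in the Kaplan-Meier analysis

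*Combined protocol and SAP*

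**What the plan says.** The synopsis (Overall Design) states: "This is a single-arm, prospective study". Section 3.2 nevertheless defines 1-year DFS as "The percentage of patients who are still alive without any evidence of disease 1 years after randomization", and the synopsis endpoint table defines 3-year DFS as "The percentage of patients who are still alive without any evidence of disease 3 years after randomization". The preoperative CRF list in section 6.1 includes "Date of randomization". The section 4 heading and section 8 also mention randomisation, but no procedure is described.

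The other clocks differ. OS in section 3.2 is "The percentage of patients who are still alive 3 years after intervention", and the synopsis (Intervention/Treatment) identifies the intervention as conversion surgery. Section 6.5 says: "Follow-up data will be collected every 6 months after surgery until patient death or the completion of the study".

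On events, section 6.5 collects death and, for disease, recurrence details beginning with "Date of recurrence". It names neither persistent disease nor progression. Section 6.2 records "Whether outcome of operation curative, palliative or unresectable". Section 7.3 plans Kaplan-Meier estimates of DFS, with log-rank and Cox analyses, and gives no origin, event list or censoring rule. Section 7.5 keeps every included eligible participant in the analysis.

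**The concern.** There are two gaps.

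First, the DFS start date cannot be obtained. The CRF field meant to hold it will be empty or filled with some other date, and the choice of that date would be made outside the plan.

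Second, a Kaplan-Meier analysis needs an event time for every failure. A patient whose tumour is not completely removed, or who has known disease elsewhere after surgery, does not meet the endpoint's condition at any time. With only recurrence and death collected, such a patient contributes disease-free time until a later recurrence is recorded. That contradicts the definition and biases DFS upward.

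Section 7.1 makes acceptable 1-year DFS/OS part of the hypothesis and anticipates a DFS/OS difference between MPR and non-MPR patients. Both would rest on an endpoint whose start and failure rule are settled after the data are known.

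**Working it through.** The plan states no DFS rate, event count or power, and section 2.2.1 says that the sample size of 30 does not come from a hypothesis test. There is therefore no figure of the plan to reproduce. The check is a sensitivity calculation.

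**Inputs from the documents**
- N = 30 (section 7.2).
- Expected R0 rate above 90% (section 7.1). 27/30 is exactly 90.0% and 28/30 is 93.3%, so an observed rate above 90% allows at most 2 non-R0 patients.
- All included eligible patients are analysed (section 7.5).

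**Will the rule be needed?** P(at least one non-R0 patient) = 1 − p^30, where p is the true R0 rate.
- p = 0.90: 1 − 0.90^30 = 95.8%.
- p = 0.95: 1 − 0.95^30 = 78.5%.

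So a rule for such patients will very probably be needed.

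**Effect of the event rule.** Assumptions: 2 of 30 are non-R0; 24 of the 28 R0 patients are disease-free at 1 year; neither non-R0 patient has a recorded recurrence or has died by then; no censoring before 1 year, so that Kaplan-Meier equals the simple proportion.
- Non-R0 patients count only on later recurrence or death: (24 + 2)/30 = 86.7%.
- Non-R0 patients count as events: 24/30 = 80.0% (exact 95% CI 61.4 to 92.3%).
- Difference: 2/30 = 6.7 points. With one non-R0 patient it would be 1/30 = 3.3 points.

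For reference, the rate among R0 patients only is 24/28 = 85.7%.

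**Effect of the origin.** Assume a constant hazard, a 1-year DFS of S from surgery, and an origin d months before surgery with no events in between. The figure at 12 months is then S^((12 − d)/12). The documents do not give the gap from enrolment to surgery; 1 week (0.23 months) to 1 month is assumed.
- S = 70%, 1 week: 0.70^(11.77/12) = 70.5%.
- S = 70%, 1 month: 0.70^(11/12) = 72.1%.
- S = 50%: 50.7% and 53.0% for the same gaps.

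The origin alone moves a 70% rate by 0.5 to 2.1 points, and a 50% rate by 0.7 to 3.0 points. The event rule matters more.

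**The case against.** The strongest defence is that the word randomisation is leftover wording and that surgery is plainly meant. The endpoint, read as a fixed-time percentage, already settles residual disease: a patient who has it at 1 year fails, which gives 24/30. Exclusion criterion 3 removes patients who cannot have a radical resection. The palliative and unresectable categories in section 6.2 are CRF options, not forecasts. DFS is secondary in an exploratory study.

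Much of this stands, and it limits the point. It does not remove it. Enrolment is as natural a substitute for randomisation as surgery is. The exclusion acts only before the operation. The fixed-time reading gives no event time for the Kaplan-Meier, log-rank and Cox analyses in section 7.3.

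A reader might infer more than the documents support:
- That the clock could start at first-line therapy and add immortal time. No section suggests that origin, and section 6.1 lists no first-line start date.
- That non-R0 patients might simply be dropped from the main DFS figure. That would breach section 7.5.
- That every patient has residual tumour at entry. Inclusion criterion 3 attaches this to the T4N0-3 or T1-3N2-3 group, not to the stage IVA clause. Tumour present before surgery does not in any case decide DFS timed from surgery.
- That the different origins spoil a comparison of OS with DFS. No such comparison is planned.

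**Conclusion.** The point holds. As written, the DFS origin does not exist, and the Kaplan-Meier analysis has no rule for patients with disease remaining after surgery. The missing rule can raise 1-year DFS by 6.7 points with 2 non-R0 patients, and by 3.3 with one, if none of them has a recorded recurrence or death by 1 year. The origin adds roughly 0.5 to 3 points over the assumed rates and gaps. The DFS rates, non-R0 counts and time gaps are illustrations, not figures from the plan.

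The 6.7 points lie well inside the confidence interval that 30 patients allow, but they are a one-directional bias and not chance. This should be fixed before analysis. It does not touch the primary endpoint, perioperative morbidity, or the sample size.

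**What to change.** 1. In section 3.2 and the synopsis, time both DFS and OS from the date of surgery.
2. Keep all operated eligible patients in DFS, in line with section 7.5. Count R1/R2 resection, exploration without resection, or known remaining disease as an event at day 0, and check that the software keeps records with time zero. Report R0-only DFS as a labelled supportive analysis.
3. State the events (day-0 failure, recurrence, death) and the censoring rule in section 7.3.
4. Replace the randomisation date on the CRF by the date of enrolment. Add margin status and residual-disease status, which sections 6.3 and 6.5 do not list.
5. Run the MPR comparison from surgery, in resected patients only.
6. Patients included but never operated have no surgery date; report their number and the reasons.

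An event-free survival endpoint from enrolment is optional. It would need a progression date, which section 6.5 does not list, and a change to section 4.3, which stops data recording for patients who withdraw before surgery.

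The cost is endpoint wording, a few CRF edits and a slightly less favourable DFS figure.
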